## Sampling

*Sample Size Calculation*

Sample size calculations were generated based on preliminary data from the Mfangano Island Healthy Network Impact Study (MIHNIS). The MIHNIS study was a quasi-experimental study with the intervention delivered to one community and neighboring communities acting as control groups. Additionally, the proposed clinic sites were visited in September 2014 to assess rates of missed clinic appointments to help ground sample size estimates in the realities of each individual clinic.

During the six months prior to delivery of the intervention in the MIHNIS study, 268 of 410 (65%) patients on ART at the Sena Health Center missed a clinic visit by >3 days. Of these, 238 (89%) joined the study. Among the control group in the MIHNIS study, 36 of 145 (25%) participants who missed a clinic visit by more than 3 days during the 6 months enrollment period had a 90-day clinic absence within the following 12 months. Among patients eligible for the intervention and who missed a clinic visit by >3 days during the enrollment period, 72 of 93 (77%) actually participated in the microclinic intervention. In the MIHNIS study participants in the intervention community had a more than 50% lower rate of 90-day disengagement than those in the control community, regardless of intervention uptake.

Thus, we assume an event rate of 0.25 in the control group and 0.125 in the intervention group. Setting alpha to 0.05 and beta to 0.2 and assuming an average of 2 participants per group with a coefficient of variation of 0.25, we will need 156 index participants per study arm. This sample size accounts for non-independence of outcomes introduced by the clustered nature of the intervention. Allowing for 10% participant attrition, we would need to sample 175 participants per study arm. The MIHNIS study ascertained outcomes for 98.6% of study participants, thus the allowance for 10% attrition in the proposed study is conservative.

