## Data Analysis

Primary analyses will be conducted using only the index study participants (i.e. participants who are HIV-infected and who missed a clinic visit by >3 days to become eligible for study participation).

Hypothesis 1

We will compare the indicence of 90-day absence from clinical HIV care between study arms using a Cox proportional hazards model. Additionally, we will depict the cumulative incidence of 90-day absence using the Cumulative Incidence Function, with death as a competing event.[24](#_ENREF_24) Primary analysis will be unadjusted, with standard errors adjusted for clustering of participants who are in the same microclinic group. Validity of the proportional hazards assumption will be assessed graphically and through formal testing using Schoenfeld residuals.

Hypothesis 2

‘Time in care’ will be calculated for each participant by subtracting the total days ‘out of care’ from the total length of follow-up and divided by the total length of follow-up. This will constitute a proportion depicting the proportion of time a given participant has spent adhering to his or her clinic appointment schedule. The number of days ‘out of care’ will be calculated by summing the total number of days between missed appointments and next clinic visits for each participant over the course of follow-up. Analysis will be conducted using linear regression to compare the mean proportion of ‘time in care’ between study arms. Standard errors will be adjusted for clustering, as in Hypothesis 1. Bootstrapping with cluster re-sampling will be conducted to address potential non-normality of residuals. Primary analysis will be conducted using unweighted time in care proportions for all participants, with sensitivity analysis conducted where each participant is weighted according to the length of follow-up.

Hypothesis 3

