Because all eligible study participants will have recently missed an appointment, we are interested in the rate of reconnection to care. Reconection to care will be defined as return to any HIV clinic and receiving a refill of that patient’s ART or co-trimoxazole prophylaxis. We will depict time to reconnection to care by study arm using the Cumulative Incidence function, with death as a competing event.[24](#_ENREF_24) We will formally test the differece in the rate of reconnection to care using a Cox proportional hazards model. Standard errors will be adjusted for clustering, as in Hypothesis 1. Validity of the proportional hazards assumption will be assessed graphically and through formal testing using Schoenfeld residuals.

Hypothesis 4

The proportion of paritipcants alive and retained in care at the end of 12 months of follow-up will be compared between study arms using simple chi-squared analysis. Retention is defined as being alive and not missing a clinic appointment by 90 days or more as of study closure at 12 months post- study enrollment.

Hypothesis 5

The proportion of participants who are alive and virally suppressed at the end of the study will be compared between study arms using chi-squared testing. Viral load testing conducted within 180 days of the 12-month timepoint post study enrollment will be used for analysis. As above, viral loads utilized for analysis will be collected during routine patient care. Primary analysis will be conducted on an intention to treat basis, with missing values assumed to be virologically non-suppressed. Sensitivity analysis will be conducted using completer analysis, where only participants with measured viral loads will be included. In this sensitivity analysis, participants who died or who disengaged from care will be included as virologically non-suppressed.

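### Retention (Hypothesis 4) and viral suppression (Hypothesis 5) are tested with plain chi-squared tests, although Hypotheses 1 to 3 allow for clustering within microclinic groups; on the plan's own inputs the effect is small

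*Protocol*

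**What the plan says.** The Data Analysis section (Protocol VIII.G) treats clustering in two ways.

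- **Hypothesis 1** (90-day absence): a Cox model "with standard errors adjusted for clustering of participants who are in the same microclinic group".
- **Hypothesis 2** (time in care): linear regression with clustered standard errors, and in addition "Bootstrapping with cluster re-sampling will be conducted to address potential non-normality of residuals".
- **Hypothesis 3** (return to care): a Cox model, where "Standard errors will be adjusted for clustering, as in Hypothesis 1".
- **Hypothesis 4** (alive and retained at 12 months): the proportions "will be compared between study arms using simple chi-squared analysis".
- **Hypothesis 5** (alive and virally suppressed): the proportions "will be compared between study arms using chi-squared testing".

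No adjustment is stated for Hypotheses 4 and 5. The Sampling section (VIII.C) says of the 156 index participants per arm: "This sample size accounts for non-independence of outcomes introduced by the clustered nature of the intervention". The Study Design Overview (VIII.F) allows one microclinic to contain more than one index patient. The Abstract says that control participants form no groups during the study, and it lists retention and suppression as secondary outcomes.

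**The concern.** All five hypotheses concern the same index participants in the same groups. A Pearson chi-squared test assumes independent observations, which the protocol says it does not have. The outcomes are also close relatives: Hypothesis 1 counts a 90-day absence, and Hypothesis 4 counts being alive without a 90-day missed appointment at closure. The plan therefore treats nearly the same behaviour as correlated within groups in one test and independent in another, and it gives no reason.

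This is not a detail left for a later analysis plan, because the protocol names the tests. An analysis plan that followed the text would carry the omission forward. At stake is whether a borderline result on retention or suppression rests on a variance that is too small.

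**Working it through.** **Inputs from the Sampling section.** The rates are p0 = 0.25 (control) and p1 = 0.125 (intervention). The mean group size is m = 2 index participants, the coefficient of variation is k = 0.25, alpha is 0.05 and power is 80%. Sidedness is not stated; two-sided is used because it reproduces the plan's figure. Event rates and correlations for retention and suppression are not given, so the 90-day absence rates stand in for them.

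**Step 1: reproduce the plan's figure.** The Hayes-Bennett formula for two proportions is

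c = 1 + (1.960 + 0.842)² × [p0(1−p0)/m + p1(1−p1)/m + k²(p0² + p1²)] / (p0−p1)²

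The bracket is 0.09375 + 0.05469 + 0.00488 = 0.15332. Divided by 0.015625 it gives 9.8125. Multiplied by 7.849 it gives 77.02, so c = 78.02 clusters per arm. With 2 per cluster this is 156 per arm, as stated. Without clustering, the usual formulas give 149 (unpooled) or 152 (pooled). The match supports two readings: the 0.25 is the between-group coefficient of variation of the outcome, and within-group correlation is built into the design.

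**Step 2: implied intracluster correlation (ICC).** ICC = (kp)²/[p(1−p)] = k²p/(1−p).

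- p = 0.25: 0.0625 × 0.25/0.75 = 0.0208
- p = 0.125: 0.0625 × 0.125/0.875 = 0.0089

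**Step 3: effect on a plain chi-squared test.** Only the intervention arm has groups. With equal arms and groups of m, the design effect in that arm is 1 + (m−1) × ICC. The true standard error is then √[(1 + design effect)/2] times the naive one, and the true error rate is 2[1 − Φ(1.96/ratio)].

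| ICC | Source | Ratio, m = 2 | True alpha, m = 2 | True alpha, m = 3 (assumed) |
|---|---|---|---|---|
| 0.0089 | plan, p = 0.125 | 1.0022 | 0.0505 | 0.051 |
| 0.0208 | plan, p = 0.25 | 1.0052 | 0.0512 | 0.052 |
| 0.05 | assumed | 1.012 | 0.053 | 0.056 |
| 0.10 | assumed | 1.025 | 0.056 | 0.062 |
| 0.20 | assumed | 1.049 | 0.062 | 0.074 |
| 0.30 | assumed | 1.072 | 0.068 | 0.086 |

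On the plan's inputs, a p-value of 0.049 from the plain test becomes 0.0495 (ICC 0.0089) or 0.0502 (ICC 0.0208).

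**Step 4: incomplete grouping.** These figures put every intervention participant in a group of two. In the pilot, 72 of 93 (77%) took part. If 77% were grouped here (an assumption), the design effect at ICC 0.0208 would be 1 + 0.77 × 0.0208 = 1.016. The ratio would be √1.008 = 1.004 instead of 1.005.

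**Step 5: power.** At 156 per arm and the 90-day absence rates, power is 81.1% ignoring clustering and 80.7 to 80.9% allowing for it at the implied ICC.

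**The case against.** The other side has several good points.

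- **Size.** On the plan's figures the error rate moves by about 0.1 percentage point. A reader might infer false-positive rates of 6 to 8%. That needs ICCs of 0.20 or more, larger groups or very uneven group sizes, and no section supports any of these. This stands.
- **Which null hypothesis.** Participants are randomised individually, and groups form afterwards (VIII.D). If the intervention changes nobody's outcome, individual allocation keeps the chi-squared test approximately valid, whatever correlation exists among friends and relatives. Inflation needs a weaker null, in which the intervention creates group-level effects that average to zero. This stands as a condition. It leaves the variance understated where the intervention does induce correlation.
- **Stratification.** Randomisation is stratified by clinic. An unstratified test is, if anything, conservative when clinics differ, so some of this small inflation may be offset. The documents do not allow that to be quantified.
- **Confidence intervals.** A reader might infer that the intervals will be too narrow. The plan states tests, and no intervals, for these two hypotheses, so that is inference.
- **Sample size.** A reader might infer that the chi-squared tests contradict the sample size. The calculation concerns 90-day absence, which is Hypothesis 1, and it does not prescribe the secondary tests. It shows only that correlation was expected.

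None of this explains why two of the five hypotheses drop an adjustment that the other three make.

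**Conclusion.** The inconsistency is real and clear on the page; its numerical effect is small. Hypotheses 4 and 5 assume an independence that the Sampling section denies and that Hypotheses 1 to 3 do not rely on. If the intervention induces positive within-group correlation, the plain tests err towards p-values that are too small. On the plan's own inputs the standard error is 0.2 to 0.5% too low, and the true alpha is 0.0505 to 0.0512.

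This rests on reading 0.25 as the between-group variation of the outcome, on 90-day absence rates as a proxy, on equal groups of two, and on clustering in the intervention arm only. The effect would be larger only if the ICC or the number of index participants per group exceeded the plan's values. Ungrouped intervention participants would make it smaller. The point is a consistency correction on two secondary outcomes, worth making because it is cheap and because the true correlation for retention and suppression is unknown.

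**What to change.** In Hypotheses 4 and 5, replace the chi-squared tests with a comparison of proportions, as a risk difference or risk ratio, with standard errors clustered on microclinic group as in Hypotheses 1 to 3. A generalised estimating equation or a generalised linear model with robust standard errors would do. State that each control participant, and each intervention participant who joins no group, is a cluster of one. Apply the same rule to the completer sensitivity analysis in Hypothesis 5.

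Adjustment for clinic is a separate choice and is not needed here; the primary analysis of Hypothesis 1 is unadjusted.

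The cost is two lines of wording and a slightly larger standard error. The sample size does not change. The replacement also gives an effect estimate, which the chi-squared test does not.

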## Project Sustainability

This project is an extension of the Mfangano Island Healthy Networks Impact Study, and thus directly a part of the sustainability of that project. As a certified Community Based Organization that has been working on Mfangano Island for the past six years, the Organic Health Response (OHR) has a longstanding commitment to the communities where this project will be implemented. Should the study demonstrate efficacy, OHR is committed to maintaining an active microclinic program on Mfangano, Remba and Ringiti islands. If efficacious, OHR plans to work with other regional and international partners to scale this intervention throughout Nyanza Province as a cost-effective and highly efficacious method for employing social networks to help maintain high levels of retention in HIV care throughout the region.

# Ethical Considerations

- 1. **Declaration of Helsinki**

The Investigators will ensure that this study is conducted in conformity to the Declaration of Helsinki and the International Conference on Harmonization.

- 1. **Institutional Review Board**

This protocol and the informed consent forms will be reviewed and approved by the ethical review bodies responsible for oversight of research conducted by the two participating institutions, KEMRI and UCSF. The IRBs in both the United States and in Kenya hold a current U.S. Federal-Wide Assurance issued by the Office for Human Research Protections (OHRP).

- 1. **Informed Consent Process**

After receiving Institutional Review Board (IRB) approval from KEMRI and UCSF and prior to the start of all study procedures, written informed consent will be obtained individually from each study participant in a private location. A written informed consent form will be provided to potential subjects in the language of his or her choice (English, Swahili or Luo; Appendex H), and its contents will be carefully and fully explained. During the written and verbal consent process, study staff will explain the purpose of the study, any anticipated consequences of the research, the anticipated uses of the data, possible benefits of the study and possible harm or discomfort that might affect participants, and the option to end the interview or study involvement at any time. In addition, it will explain the secure, confidential storage of the data, and explain that participants will receive access to the aggregate final results of the study. All participants will be over 18 years old and will have the capacity to consent for themselves. In the event that a potential participant is illiterate, the participant will mark his/her thumbprint and a witness will be asked to preside over the consenting process and co-sign the consent form.

- 1. **Subject Confidentiality**

Participant confidentiality is of paramount importance to the study investigators and staff and extreme caution will be taken to avoid any breaches of confidentiality. Study staff will be thoroughly trained in research practices and confidentiality, as well as proper handing of study documents. Data collected from participants will be de-identified at the time of data collection and will only be linked to identifying information through the unique study ID. As discussed above, identifying information and study datasheets will be kept in separate locked file cabinets located in a locked room dedicated only for research activities.

Participants will be advised that, by nature, group interventions such as the microclinic intervention have an inherant risk that confidentiality will be breached by a fellow group member. To minimize this risk, a substantial portion of the microclinic curriculum focuses on the importance of creating a safe space for all group members, emphasizing that all discussion that occurs within the setting of the group must not be shared with those outside the group.

- 1. **Study Discontinuation**

Inadaquate participant enrollment is the only reason why the study will be prematurely discontinued. Inadequate enrollment is defined as <50 participants enrolled in the study at the end of the 6 month enrollment period.

- 1. **Alternatives to Study Participation**

The alternative to study participation is not to participate. This will not in any way affect potential patients’ access to benefits from FACES or OHR services.

- 1. **Risks and Benefits of Study**

1. **Potential risks and discomforts**

The main risk of this study is breach of confidentiality or harm to reputation resulting from unintended HIV status disclosure.

1. **Steps being taken to minimize potential risks or discomforts**

Both study staff and microclinic group members will be trained on the importance of maintaining confidentiality. Additionally, all study documents will be de-identified at the time of data collection and stored separately from identifying information.

1. **Potential direct benefits to study subjects**

There is no direct benefit to study subjects. The intervention may provide benefit, but as there is currently equipoise regarding the efficacy of this intervention, this cannot be considered a benefit.

1. **Potential benefits to society**

This study evaluates a novel, sustainable, community-based intervention for improving clinical HIV care. If the intervention proves successful, the intervention will be expanded to include all patients meeting criteria at the study sites. If adopted by other clinical sites, it could also have broader impact on HIV service delivery throughout the region.

Furthermore, this intervention evaluates a method for improving clinical care that could be applied to other health problems beyond HIV. Our research group has evaluated this model for diabetes care in other parts of the world and, similarly, is interested in expanding the scope of its use for other chronic illnesses or health challenges that involve a behavioral component in their treatment.

1. **Risk/Benefit analysis**

The risks of this study are minimal, especially after careful attention to minimizing such risks taken by the study team. Conversely, the potential benefits to society are great. Should this intervention prove effective, it will pave the way for broad implementation across Mfangano, Ringiti and Remba islands, at minimum. If adopted by study team partners, it could also impact the way that HIV patients are supported throughout Nyanza. Our assessment is that the benefits outweigh the risks in this case.

1. **Payments to subjects**

Participants who have missed clinic visis at either baseline or end-of-study visits will receive 100 shillings to compensate participants for time spent responding to survey questions. Investigators have choosen to offer this small monitary reimbursement because it is consistent with what other studies in the region are also providing to participants (i.e. the SEARCH study). Subjects who participate in a microclinic group will receive refreshments at group meetings (tea and mandazi) as both an incentive to attend group meetings and as a symbol of group solidarity.

1. **Cost to subjects**

The only cost to subjects is their time. The pre- and post-intervention surveys will take approximately 30 minutes each.

# Data Management

- 1. **Data Collection and Storage**

Survey data will be collected by bilingual OHR research staff and recorded electronic tablets using Open Data Kit. Data entered into tablets will not contain any identifying information and tablets will be password protected. The limited personal identifying information collected from participants (name, date of birth, and a unique study identification number) will be written on a paper datasheet, which will be linked to data in the tablet only through the use of the unique study ID number. Identifier pages and tablets will be stored in separate locked containers immediately following data collection.

Data collected through the tablets will be encrypted and uploaded to a secure server. Identifying information will be entered into a separate Microsoft Access database and this ‘link log’ will be maintained on a password protected computer located in a locked room at the study site. Data collected from clinics included in the study will be entered into a password protected Microsoft Access database located on a dedicated, password-protected study computer. The study database will be backed up on the secure UCSF MyResearch portal.

- 1. **Data Analysis**

Study investigators will be responsible for all data analysis. Analysis will be conducted in Stata and will consist of intent-to-treat comparison of study outcomes between study arms.

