The microclinic intervention includes participation by members of the index patient’s social network. This may include other index patients, or community members who are HIV-infected, HIV-uninfected or of unknown HIV status. These non-index microclinic members, referred to as ‘social network’ participants, will be invited to join the study in addition to participation in a microclinic group. Microclinic participant is not contingent on study participation, however data will only be collected for microclinic group members who also consent to study participation.(Appendix I) For social network participants, study participation involves completion of a baseline survey to collect information on sociodemographic characteristics, HIV-related stigma, previous HIV testing, HIV status, and enrollment and engagement in HIV care (if HIV-infected).(Appendix D) For each microclinic group, a Microclinic Group Member Information form will also be completed to describe the nature of the realtionships between group members.(Appendix E) Only group members who consented to study participation will be included. At the time of group enrollment, all prospective social network study participants will be invited to enroll in the study. Following study enrollment, these surveys to collect information on sociodemographic characteristics and HIV-related stigma will be administered by trained study staff. Data on previous HIV testing, HIV status and enrollment and engagement in HIV care will be collected by a trained Voluntary Counseling and Testing (VCT) counselor as part of a baseline HIV counseling and testing session. Refusal to participate in the study will not preclude social network group members from participating in the microclinic group, but no study data will be collected on these participants.

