### Data Verification and Security

All data will be collected by study staff trained in Good Clinical Practice procedures and Human Subjects Protection. Training will be conducted independently by an on-site co-investigator and through internet-based courses with the NIDA Clinical Trials Network and the National Institutes of Health. Training will be renewed on an annual basis during the duration of the trial.

All personal identifying information (name, date of birth, phone number, locator information, medical record number) will be collected on a hard copy form that will be separate from the rest of the survey data that will be collected on elecronic tablets. Identifying information will be linked to electronically-captured study data only through a unique identifier that is assigned by the study and carries no meaning outside the study. Indentifying information will be stored in separate locked file cabinets in the Ekialo Kiona Center Research Department. De-identified electronic data will be collected using password protected tablets and will be encrypted and uploaded to a secure server. Tablets will be stored in the study office, which will remain locked any time an authorized study staff member is not present. Furthermore, the Ekialo Kiona center is under survelliance 24 hours per day, 7 days per week by a trained security guard to ensure that there is no unauthorized access to the facilities or to confidential research documents.

Data collected at the health facilities will be entered into a password-protected Microsoft Access database on a password protected laptop. Where possible, clinical data will be cross-checked against electronic medical record data obtained from the FACES OpenMRS database.

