| Person Code | a. Name | *b.* M*ale or female?*  1 = Male  2 = Female | *c. How old is he/she?*  |__|__|  Years | *d. What is this person’s relationship with you?*  2 = WIFE/HUSBAND/LIVE-IN  PARTNER  3 = SON OR DAUGHTER  4 = SON/DAUGHTER-IN-LAW  5 = GRANDCHILD  6 = PARENT  7 = PARENT-IN-LAW  8 = BROTHER OR SISTER  9 = NIECE/NEPHEW  10 = AUNT/UNCLE (brother/sister to your parent)  11 = CLOSE FRIEND  12 = BUSINESS ASSOCIATE  13 = AQUAINTANCE  15 = OTHER specify: | *e. If you were to form a kanyakla, would you want this person in your group?*  *0 – No*  *1 – Yes*  *2 – Unsure* | *f. Without telling me whether they are negative or positive, do you know this person’s HIV status?*  *0 – No*  *1 – Yes*  *88 – Decline to answer* | *g. Does this person know your HIV status?*  *0 – No*  *1 – Yes*  *88 – Decline to answer* | h. How much material support does this person offer you? (including financial assistance, food, school fees, etc.)  0 – None  1 – a little  2 – moderate  3 – quite a bit  4 – a great deal | i. How much emotional support does this person offer you? (including love/friendship, comfort, advice, and counseling)  0 – None  1 – a little  2 – moderate  3 – quite a bit  4 – a great deal | j. How much does support from this person help you attend you clinic appointments?  0-None  1-Not often  2-Somewhat often  3-Often  4-Everytime | k. How much does support from this person help you to take your HIV medication?  0-None  1-Not often  2-Somewhat often  3-Often  4-Every dose |
| 01 |  | 1 2 | |__|__|   DK |  | 0 1 2 | 0 1 88 | 0 1 88 |  |  |  |  |
| 02 |  | 1 2 | |__|__|   DK |  | 0 1 2 | 0 1 88 | 0 1 88 |  |  |  |  |
| 03 |  | 1 2 | |__|__|   DK |  | 0 1 2 | 0 1 88 | 0 1 88 |  |  |  |  |
| 04 |  | 1 2 | |__|__|   DK |  | 0 1 2 | 0 1 88 | 0 1 88 |  |  |  |  |
| 05 |  | 1 2 | |__|__|   DK |  | 0 1 2 | 0 1 88 | 0 1 88 |  |  |  |  |
| 06 |  | 1 2 | |__|__|   DK |  | 0 1 2 | 0 1 88 | 0 1 88 |  |  |  |  |
| 07 |  | 1 2 | |__|__|   DK |  | 0 1 2 | 0 1 88 | 0 1 88 |  |  |  |  |
| 08 |  | 1 2 | |__|__|   DK |  | 0 1 2 | 0 1 88 | 0 1 88 |  |  |  |  |
| 09 |  | 1 2 | |__|__|   DK |  | 0 1 2 | 0 1 88 | 0 1 88 |  |  |  |  |
| 10 |  | 1 2 | |__|__|   DK |  | 0 1 2 | 0 1 88 | 0 1 88 |  |  |  |  |

| **SECTION E. SUPPORT FOR HIV CARE** | | | | | | |
| --- | --- | --- | --- | --- | --- | --- |
| **Please evaluate the following statements:** | | | | | | |
|  | **Never** | **Not often** | **Somewhat often** | | **Often** | **Every time/ every dose** |

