| Person Code | a. Name | *b.* M*ale or female?*  1 = Male  2 = Female | *c. How old is he/she?*  |__|__|  Years | *d. What is this person’s relationship with you?*  2 = WIFE/HUSBAND/LIVE-IN PARTNER  3 = SON OR DAUGHTER  4 = SON/DAUGHTER-IN-LAW  5 = GRANDCHILD  6 = PARENT  7 = PARENT-IN-LAW  8 = BROTHER OR SISTER  9 = NIECE/NEPHEW  10 = AUNT/UNCLE (brother/sister to your parent)  11 = CLOSE FRIEND  12 = BUSINESS ASSOCIATE  13 = AQUAINTANCE  15 = OTHER specify: | *e. Was this person in your Kanyakla?*  *0 – No*  *1 – Yes*  *2 – I am not in a kanyakla* | *f. Without telling me whether they are negative or positive, do you know this person’s HIV status?*  *0 – No*  *1 – Yes*  *88 – Decline to answer* | *g. Does this person know your HIV status?*  *0 – No*  *1 – Yes*  *88 – Decline to answer* | h. How much material support does this person offer you? (including financial assistance, food, school fees, e.t.c.)  0 – None  1 – a little  2 – moderate  3 – quite a bit  4 – a great deal | i. How much emotional support does this person offer you? (including love/friendship, comfort, advice, and counseling)  0 – None  1 – a little  2 – moderate  3 – quite a bit  4 – a great deal | j. How much does does support from this person help you attend you clinic appointments?  0-None  1-Not often  2-Somewhat often  3-Often  4-Everytime | k. How much does does support from this person help you to take your HIV medication?  0-None  1-Not often  2-Somewhat often  3-Often  4-Every dose |
| 01 |  | 1 2 | |__|__|   DK |  | 0 1 2 | 0 1 88 | 0 1 88 |  |  |  |  |
| 02 |  | 1 2 | |__|__|   DK |  | 0 1 2 | 0 1 88 | 0 1 88 |  |  |  |  |
| 03 |  | 1 2 | |__|__|   DK |  | 0 1 2 | 0 1 88 | 0 1 88 |  |  |  |  |
| 04 |  | 1 2 | |__|__|   DK |  | 0 1 2 | 0 1 88 | 0 1 88 |  |  |  |  |
| 05 |  | 1 2 | |__|__|   DK |  | 0 1 2 | 0 1 88 | 0 1 88 |  |  |  |  |
| 06 |  | 1 2 | |__|__|   DK |  | 0 1 2 | 0 1 88 | 0 1 88 |  |  |  |  |
| 07 |  | 1 2 | |__|__|   DK |  | 0 1 2 | 0 1 88 | 0 1 88 |  |  |  |  |
| 08 |  | 1 2 | |__|__|   DK |  | 0 1 2 | 0 1 88 | 0 1 88 |  |  |  |  |
| 09 |  | 1 2 | |__|__|   DK |  | 0 1 2 | 0 1 88 | 0 1 88 |  |  |  |  |
| 10 |  | 1 2 | |__|__|   DK |  | 0 1 2 | 0 1 88 | 0 1 88 |  |  |  |  |

| **SECTION F. SUPPORT FOR HIV CARE** | | | | | | |
| --- | --- | --- | --- | --- | --- | --- |
| Please evaluate the following statements: | | | | | | |
|  | Never | Not often | Somewhat often | | Often | Very Often |

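### The social-network rosters in the baseline and end-of-study surveys record contacts' names beside HIV-disclosure answers under a study ID, although the protocol says tablet data hold no identifiers

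*Protocol*

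**What the plan says.** The safeguards are stated in three places in the protocol.

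- **Section VIII.F, Data Verification and Security.** Name heads the list of personal identifiers. These "will be collected on a hard copy form that will be separate from the rest of the survey data", and the survey data themselves go on tablets.
- **Section IX, Ethical Considerations.** Under Subject Confidentiality: "Data collected from participants will be de-identified at the time of data collection". Under risks: "The main risk of this study is breach of confidentiality or harm to reputation resulting from unintended HIV status disclosure". Two protective steps follow: training in confidentiality, and the commitment that "all study documents will be de-identified at the time of data collection and stored separately from identifying information".
- **Section X, Data Management.** Surveys are recorded on tablets in Open Data Kit, and "Data entered into tablets will not contain any identifying information and tablets will be password protected". Name, date of birth and study ID go on a paper sheet.

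The forms are in the English Appendices. The baseline survey (Appendix C, Section D) and the end-of-study survey (Appendix G, Section E) each contain a ten-line roster of people important to the respondent. Both rosters have a Person Code column and a Name column, and both ask of each contact: "Does this person know your HIV status". The end-of-study roster also asks: "Was this person in your Kanyakla".

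On group members who are not index participants, the Study Design Overview says that "data will only be collected for microclinic group members who also consent to study participation". The Subject Recruitment and Enrollment section allows one exception for people who decline: their reasons for refusing.

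**The concern.** The protocol fixes both the promise and the instruments, and they do not agree. Used as printed, the rosters put names into the same record as the study ID and the disclosure answers. The names belong to contacts, not to the respondent. Even so, a spouse, children and siblings listed by name, age and relationship can point to the respondent in a small island community. Both surveys ask how the respondent feels about being HIV positive, so recognising the respondent reveals HIV status. The roster further shows which named people already know it.

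What is at stake is confidentiality, the hazard the protocol itself ranks first. No endpoint, estimate or power figure is affected.

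**Working it through.** The protocol gives no figure to reproduce for this point. The check sets the safeguards against the fields of each form.

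| Form | Study ID | Name | HIV-disclosure answers | Limited to people who consented |
| --- | --- | --- | --- | --- |
| Baseline survey, Section D | Yes (header) | Yes, up to 10 contacts | Yes, same row | No |
| End-of-study survey, Section E | Yes (header) | Yes, up to 10 contacts | Yes, same row | No |
| Group information form (Appendix E) | Yes, same row | Yes | None | Yes (Study Design Overview) |
| Group member survey (Appendix D) | Yes | None | Yes, with test result | Yes |

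1. **Rosters against the tablet rule.** Section X puts survey data on tablets and excludes identifying information from them. Section VIII.F counts name as such information. Nothing exempts the Name column, so the two rosters conflict with the rule.
2. **If the names stayed on a paper copy of the survey.** That would satisfy the tablet sentence. The Section IX commitment covers all study documents, so a survey form with names beside disclosure answers would still conflict with it.
3. **Appendix E.** It pairs Name with Participant ID, along with gender, age, relationship codes, group name and meeting location. It has no HIV field. Because the group member survey is keyed by the same ID and holds a test result, Appendix E can act as a key to it. Its storage therefore matters, and the protocol does not say where the form is kept.
4. **People who declined enrolment.** They may still attend a group. Appendix G item e asks about group membership for every listed person and has no consent condition, so an intervention-arm respondent can name someone who declined and mark that person as a member. The baseline roster is completed at enrolment, before the respondent's own group exists, so it generally does not raise this problem.
5. **Scale.** The Sampling section allows up to 180 participants per arm: 180 × 2 = 360. Each roster has 10 lines: 360 × 10 = 3,600 rows at most in each survey round. This assumes full enrolment, every line filled and, at closure, every participant surveyed.

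**The case against.** The strongest reply is that the appendices are printed templates. Person Code is already there, Section X puts names on paper, and the Name column may be only an interview prompt that never reaches the tablet. The respondent's own name is on the separate locator form, as planned. Tablet data are encrypted on upload, the devices are password protected, and storage is locked. Item f tells the respondent not to say whether a contact is positive or negative, so contacts' HIV status is not recorded.

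Most of this is accurate and limits the likely harm. It does not remove the contradiction, because the protocol nowhere says the names are left off.

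A reader might also infer three stronger things that the documents do not support.

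- **That Appendix E sets names beside HIV answers and includes people who refused.** It has no disclosure column, and the Study Design Overview restricts it to consenting members. Groups mix infected, uninfected and unknown-status members, so a row does not by itself reveal status.
- **That Appendix E is an unprotected second link log.** The protocol is silent on its storage, and silence does not show that it is unsecured. Section X itself plans a paper sheet holding name and study ID, and the protocol keeps identifying information in locked storage.
- **That 3,600 counts refusers or breaches.** Most listed contacts may never have been invited to a group, and control participants form none during the study. The number who decline is unknown.

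**Conclusion.** The contradiction stands for the two survey rosters. Sections VIII.F, IX and X promise de-identified survey data, while Appendix C Section D and Appendix G Section E collect contacts' names with sex, age, relationship and disclosure answers under a study ID. The ceiling is 3,600 rows per survey round.

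The conclusion assumes that the forms are used as printed. The view that a roster can reveal its respondent is a judgement about a small community; the documents give no basis for a probability.

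Two lesser matters remain. The storage of Appendix E is unstated. Appendix G item e can also capture a named person who declined enrolment, which does not sit with the promise to hold nothing on such people beyond their reasons for refusing. A correction is worthwhile because it is cheap and makes a stated protection against the main named risk true.

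**What to change.** 1. Remove the Name field from the tablet version of both rosters and enter only the Person Code. Keep the code-to-name list on the separate locked paper identifier page described in Sections VIII.F and X, and use the same codes at closure so that the two rounds can be matched.
2. State that Appendix E is stored with the identifying documents. Keep its Name column, because staff need it to complete the relationship grid.
3. Reconcile Appendix G item e with the commitment on people who decline enrolment. If answers about them are to be dropped, do it at data management. The end-of-study script has interviewers say they have not been told who was offered a group, and a consent look-up during the interview could reveal allocation.

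The cost of the first change is one paper code list per participant, which must be kept secure and retrieved at closure. It loses no analysis variable. A consent filter on item e would remove some reported group members from the network data, so the protocol should say whether that is intended.
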